### Statistics

For each trial (*n* = 50), ERD and ERS modulations will be computed in the 8–30 Hz frequency band for the [–2;6]s time window. This time window was chosen according to the ERD occurrence during the motor task (i.e., 2 s for RM, MI, and MI+MNS) and the time required for the ERS to return to the baseline [21]. For each trial, an ERD max and an ERS max will be selected in both their respective time windows ([0;2]s and [4;6]s). For the MNS task, in accordance with the literature [26, 27], the ERD ERS max will be respectively selected in [0.25;0.5]s and [2;4]s after stimulation. An average over the 50 ERDs max and 50 ERSs max will be performed for the motor tasks (MR, MI, MNS, MI+MNS) and each concentration (0 *μ*g.ml ^−1^, 0.5 *μ*g.ml ^−1^, and 1 *μ*g.ml ^−1^). These two values will be compared with each other for each motor task during the three concentrations with a Student’s *t* test (*p* value <0.05).

The ERD and ERS will also be visualized as event-related spectral perturbations (ERSPs). ERSPs allow one to visualize event-related changes in the average power spectrum relative to a baseline of 1.5 s taken 2 s before the auditory cue for all motor tasks and different propofol concentrations [39]. A surrogate permutation test (*p* <0.05; 2000 permutations) from the EEGLAB toolbox will be used to validate differences in terms of time-frequency of this ERSPs. In addition to this analysis, we will apply a false discovery rate (FDR) correction test in order to clarify how the FDR will be controlled for multiple comparisons. This test consists of repetitively shuffling values between conditions and recomputing the measure of interest using the shuffled data. It will be performed by drawing data samples without replacement and is considered suitable to show the difference for all motor tasks during different concentrations of propofol [40].

Finally, we will compute the performance of four different classification methods in a fourfold cross-validation scheme. The first one uses a linear discriminant analysis (LDA) classifier trained and evaluated using common spatial pattern (CSP) features generated from the first and last four CSP filters [41] (referred to as CSP+LDA). The CSP method is widely used in the field of MI-base BCI, as it provides a feature projection onto a lower dimensional space that minimizes the variance of one class while maximizing the variance of the other. The other three classifiers are Riemannian geometry-based classification methods. Riemannian geometry-based methods work with the covariance matrices of each trial, which lie on the Riemannian manifold of symmetric positive definite matrices. These features have therefore the advantage of being immune to linear transformations [42] We chose to apply a paired *t* test (two-sided) to show the significant difference in accuracy obtained for MI versus Rest and MI + MNS versus Rest with the TS + LR classifier (at *p* values <0.05).

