**Fig. 2 Fig2:**
[figure not shown]
Flowchart of experimental scheme. The healthy volunteer subject will be lying down and fitted with an EEG helmet with 128 sensors, 32 of which will be placed at the level of the motor cortex. The signals will be recorded using the OpenViBE software. The infusion of propofol will be performed by an infusion pump with a concentration target

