***Getting closer to the anesthetized state***

Since the first reflex for a patient during an AAGA is to move, a passive BCI based on the intention of movement is conceivable. Indeed, Blokland et al. have shown the feasibility of such a device [24]. However, the challenge of using such a BCI is that the intention to move from the waking patient is not initiated by a trigger that could be used to guide a classifier. In a previous study, we proposed a new solution based on MNS, which causes specific modulations in the motor cortex and can be altered by an intention of movement. We showed that MNS may provide a foundation for an innovative BCI that would allow the detection of an AAGA [23]. More particularly, we verified that MNS modulates the motor cortex by first generating an ERD during stimulation and then an ERS post-stimulation in voluntary subjects. In addition, we have discovered a new post-stimulation rebound ERS (PSR) which appears 250 ms after the stimulation in the mu and low beta bands. MNS combined with the intention to move, i.e., the MI, had a significant impact on the ERD and ERS generated by the MNS. Indeed, despite the fact that the ERD was unaltered, the PSR was almost abolished and the rebound in the beta band was diminished. Those differences have allowed a classification with highly accurate results. With these findings, we showed that a BCI based on MNS is more effective than a BCI based on a MI state versus rest [23]. Our results will be confirmed during the MOTANA clinical protocol, where the same conditions will be used on voluntary subjects sedated with propofol.

If we can find similar results in propofol-sedated subjects, we will plan to repeat the experimentation on subjects under general anesthesia with neuromusclar blockade in order to study RM intention instead of motor imagination. In a final experiment, we could combine both conditions with paralyzed and anesthetized patients in order to investigate if the combination could change the results.

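### With 2000 permutations followed by an FDR correction, an isolated time-frequency effect covering less than about 1% of the FDR family cannot be declared (minor)

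*Protocol article*

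**What the plan says.** The Statistics section compares averaged ERD and ERS maxima between propofol concentrations by t test. In addition, it displays the responses as ERSP maps and tests differences between maps by permutation: "2000 permutations) from the EEGLAB toolbox will be used to validate differences in terms of time-frequency of this ERSPs", at p < 0.05. It describes the resampling as follows: "This test consists of repetitively shuffling values between conditions and recomputing the measure of interest using the shuffled data". Multiplicity is handled by one sentence: "we will apply a false discovery rate (FDR) correction test in order to clarify how the FDR will be controlled for multiple comparisons".

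The article does not give the FDR procedure, its level, the family of tests, the ERSP grid, the tail, or how p is formed when no permutation reaches the observed value. An article may leave such details to a fuller document, and their absence is not the point here. The permutation count is fixed, and the point concerns that count.

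Three other statements bear on the size of the effects. The amplitude analysis uses this band and window: "ERD and ERS modulations will be computed in the 8–30 Hz frequency band for the [–2;6]s time window". For stimulation alone, "ERD ERS max will be respectively selected in [0.25;0.5]s and [2;4]s after stimulation". The Discussion describes a further post-stimulation rebound "which appears 250 ms after the stimulation in the mu and low beta bands".

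**The concern.** Two thousand permutations are ample for a single test at 5%: the Monte Carlo standard error at p = 0.05 is √(0.05 × 0.95/2000) = 0.0049. An FDR correction over a map asks for more, because the first Benjamini-Hochberg thresholds lie far below 0.05 and a permutation p value cannot go below 1/(B+1). An effect on a small part of the map may then fail however strong it is. The alternative of letting p equal zero avoids that limit but gives up error control.

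The brief responses to median nerve stimulation are the ones at risk, and the proposed monitoring concept rests on stimulation. The early rebound matters most. It is a synchronization starting at about 250 ms, whereas the ERS maxima for the t tests are taken in [2;4] s for stimulation alone and [4;6] s for the other tasks. No amplitude t test therefore measures the rebound in its own time range, which leaves the ERSP map as the planned concentration comparison that could show it.

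**Working it through.** The article derives no figure from the 2000 permutations, so there is nothing to reproduce.

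**Inputs from the article.** B = 2000; an 8-s window ([–2;6] s) and a 22-Hz band (8–30 Hz), used here as the size of the map; stimulation ERD window 0.25 s; stimulation ERS window 2 s; mu 7–13 Hz, of which 5 Hz lie within 8–30 Hz; beta 15–30 Hz; 128 channels, 32 over the motor cortex.

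**Assumed.** Benjamini-Hochberg at q = 0.05; p = (b+1)/(B+1), where b is the number of permutations reaching the observed value; selection windows taken as response durations.

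**Floor.** Of m points, k tied at the smallest p are declared if k·q/m ≥ 1/(B+1).
- B = 2000: k/m ≥ (1/2001)/0.05 = 0.0004998/0.05 = 1.00%.
- B = 20,000: (1/20,001)/0.05 = 0.10%.
- Two-sided p formed by doubling a tail, B = 2000: 2.00%.

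**Share of one channel's 8 s × 8–30 Hz map.**
- Stimulation ERD, mu only: 0.25/8 × 5/22 = 0.71%, below the floor.
- Stimulation ERD, beta only: 0.25/8 × 15/22 = 2.1%.
- Stimulation ERD, full band: 0.25/8 = 3.1%.
- Stimulation ERS, beta: 2/8 × 15/22 = 17%; full band: 2/8 = 25%.
- Early rebound, assuming 0.25 s and 8–20 Hz: 0.25/8 × 12/22 = 1.7%.

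The EEG data acquisition section gives the epoch as 9 s and also as 1 s before to 5 s after the task. The mu-only share is 0.63% of a 9-s map and 0.95% of a 6-s map, so it stays below 1% either way.

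If all 128 channels form one family and the effect lies on the 32 motor channels, each share is multiplied by 32/128. The full-band stimulation ERD becomes 0.78% and the assumed rebound 0.43%.

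**Simulation, 20,000 independent points, 400 runs, B = 2000, p = (b+1)/(B+1).** The effect is too large for any permutation to reach.

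| Effect share | Other strong effect | Declared |
|---|---|---|
| 0.71% | none | 0% |
| 0.95% | none | 48% |
| 1.05% | none | 100% |
| 0.71% | 0.5% | 100% |
| 0.1% | 17% | 100% |

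**Simulation, one smoothed (correlated) 8 s × 8–30 Hz map, 30 subjects.** A lone mu-only 0.25-s effect was detected in about 1% of runs at 2000 permutations and in 100% at 20,000.

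**If p = b/B.** A null point has probability 1/2001 of p = 0 and then always survives. With no true effect and m independent points, the chance of at least one false point is 1 − (2000/2001)^m: 10% for m = 200 and 39% for m = 1000. On the smoothed map, a false declaration occurred in 55% of maps at 2000 permutations and 4% at 20,000. In the 20,000-point simulation, a true effect on 0.25% of points was always declared, with a false discovery proportion of about 16%.

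**The case against.** The limit depends on choices the article does not state. On the only window and band it gives, taken channel by channel, the full-band stimulation ERD (3.1%) and the assumed rebound (1.7%) both clear 1%. Only the mu-confined case falls below it; the other small shares need channel pooling, a wider frequency axis or doubled tails. The durations are also assumed: [0.25;0.5] s is where a maximum is picked, and only an onset is given for the rebound. The ERSP maps supplement t tests that have no permutation floor, and one of those tests covers the stimulation ERD. All of this stands and limits the size of the point. It does not remove it, because at 2000 permutations one p-value convention costs power for small isolated effects and the other costs FDR control.

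A reader might infer that brief stimulation responses cannot be declared at any size. The documents do not support that. The floor counts every point at the smallest p in the family. If propofol also changes the 2-s stimulation ERS, which spans 17–25% of the same map, the brief effect is declared too; whether it does is unknown. A reader might also infer near-certain false findings under p = b/B over a large map. That follows only for very many independent points, and neighbouring time-frequency points are correlated.

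**Conclusion.** The point holds as a minor one. Under Benjamini-Hochberg at 5% with p = (b+1)/(B+1), 2000 permutations cannot declare an isolated effect on less than about 1% of the family, unless other strong effects bring the total share at the smallest p to about that level. A mu-confined 0.25-s stimulation effect, at about 0.7% of one channel's map, is a plausible case. With p = b/B there is no floor, but the FDR is not controlled. Both statements rest on the assumed FDR variant, level, family and response durations.

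What is affected is a supplementary analysis in an exploratory study. The stimulation ERD keeps a t test without this limit. The early rebound has no amplitude t test in its time range, so the resolution of the ERSP test matters more for it, although its share of the map cannot be fixed from the article.

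**What to change.** Raise the count to about 20,000 permutations, compute p as (b+1)/(B+1), and state that the FDR is applied separately for each task and concentration contrast over the motor-cortex channels. The floor falls to 0.10% of the family. For a mu-only effect this means at least 5 of the 32 motor channels (0.71% × 5/32 = 0.11%). The 0.71% share alone needs only about 2,816 permutations, so 20,000 leaves room for a wider frequency axis, doubled tails or fewer affected channels. The cost is computing time and one sentence in the analysis plan; the data collected do not change.

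Optionally, keep 2000 permutations and replace pointwise FDR with a cluster-mass or maximum-statistic permutation test, neither of which needs p values far below 0.05. With cluster mass, significance attaches to the cluster and not to each time-frequency point.

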**Methods:**

MOTANA is an interventional, prospective, exploratory, physiological, monocentric, and randomized study conducted in healthy volunteers under light anesthesia, involving EEG measurements before and after target-controlled infusion of propofol at three different effect-site concentrations (0 *μ*g.ml ^−1^, 0.5 *μ*g.ml ^−1^, and 1.0 *μ*g.ml ^−1^). In this exploratory study, 30 healthy volunteers will perform 50 trials for the four motor tasks (real movement, motor imagery, motor imagery with median nerve stimulation, and median nerve stimulation alone) in a randomized sequence. In each conditions and for each trial, we will observe changes in terms of ERD and ERS according to the three propofol concentrations. Pre- and post-injection comparisons of propofol will be performed by paired series tests.

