During an AAGA, there is evidence that the patient’s first reflex is to move to warn the surgical team [16]. However, patients may desperately attempt to move, without success [17] and perform a so-called intention to move. A motor imagery (MI) can be detected by recording the EEG signal over the motor cortex such as in the brain-computer interface (BCI) domain [18, 19]. Indeed, the mu (7–13 Hz) and beta (15–30 Hz) sensorimotor rhythms are characterized, before and during a MI, by a gradual decrease of power in mainly the alpha (mu) and beta bands, and after the end of the MI, by an increase of power in the beta band. These modulations are respectively known as event-related desynchronization (ERD) and event-related synchronization (ERS) or post-movement beta rebound [20–22].

If a BCI based on the MI of a patient seems feasible [23], the impact of propofol on the EEG activity, especially over the motor cortex, is still not yet fully understood. In 2016, Blokland et al. studied the effect of propofol on voluntary subjects who performed movements according to sound beeps while an increasing dosage of anesthetic was administered to them [24]. The authors described the impact of propofol on the EEG signal and showed how the BCI domain could contribute to the issue of AAGAs, but they emphasized that this approach is not a realistic situation, since the patient is explicitly asked to perform a movement. To address this issue, we have shown in a previous article that a frequent stimulation of the median nerve is a very promising approach [23]. Indeed, previous studies have shown that a painless stimulation of the median nerve induces an ERD during the stimulation while an ERS appears after the stimulation [25, 26]. Our recent study showed that a MI was more effectively detected using a median nerve stimulation (MNS). This result highlights promising classification results that would allow us to create a reliable device which can be used in the operating room. Therefore, we can imagine a routine system where the median nerve of the patient would be stimulated, and the analysis of ERD and ERS modulations of the motor cortex would be used to know if the patient has an intention to move. However, this study was conducted without propofol, and the previous results obtained need to be confirmed. The study we propose in this clinical protocol will provide the missing answers to these questions and provide insights into the design of such a BCI.

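### The one named accuracy test sets MI + MNS against unstimulated Rest, so a gain over MI versus Rest could come from the stimulus alone and would not show that movement intention is detected

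*Protocol article*

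**What the plan says.** The Statistics section of the protocol article ends with the evaluation of "four different classification methods in a fourfold cross-validation scheme". The one inferential comparison of accuracy named there is a two-sided paired t test, at the 0.05 level, of the "significant difference in accuracy obtained for MI versus Rest and MI + MNS versus Rest with the TS + LR classifier".

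On the stimulus, the Background reports that "a painless stimulation of the median nerve induces an ERD during the stimulation while an ERS appears after the stimulation". The Discussion (Getting closer to the anesthetized state) says of the sponsor's earlier study that "MNS modulates the motor cortex by first generating an ERD during stimulation and then an ERS post-stimulation in voluntary subjects". It adds that "MNS combined with the intention to move, i.e., the MI, had a significant impact on the ERD and ERS generated by the MNS": the early rebound after stimulation nearly disappeared and the beta rebound shrank. It credits these differences with the accurate classification.

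On the intended use, the Background says "we can imagine a routine system where the median nerve of the patient would be stimulated", with the ERD and ERS modulations then read for an intention to move.

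On the data, "30 healthy volunteers will perform 50 trials for the four motor tasks". MNS alone is one of those tasks and is recorded at each of the three propofol concentrations (Study design; Fig. 1 legend). The resting state appears in the Fig. 1 legend and the Study design as the period that follows the task. No stimulation is described in it.

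**The concern.** In MI + MNS versus Rest, two things differ between the classes: the imagery and the electrical stimulus. In MI versus Rest, only the imagery differs. A classifier given the first pair can use the stimulus response, so a gain over the second pair is to be expected whether or not imagery adds anything.

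In the device that the article envisages, the nerve is stimulated routinely. The state to be told apart from an attempt to move is therefore stimulation without that attempt, not rest without stimulation. The contrast that matches this is MI + MNS versus MNS alone, and it is also where the Discussion itself locates the intention signal.

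What is at stake is interpretation. A significant result of the planned test could be read as support for detecting intention under propofol, and could be carried into the follow-up experiments under general anesthesia, when it shows only that the stimulus is visible in the EEG.

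**Working it through.** **The plan's own figure.** None exists for this comparison. The article gives no expected accuracy, SD, effect size or power, so there is nothing to reproduce.

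**Step 1: what differs between the classes.**

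| Contrast | Imagery differs | Stimulus differs | Named for an accuracy test |
|---|---|---|---|
| MI vs Rest | yes | no | yes |
| MI + MNS vs Rest | yes | yes | yes |
| MI + MNS vs MNS | yes | no | no |

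The two named contrasts differ from each other by the presence of the stimulus. The paired t test on their difference therefore cannot separate a stimulus effect from an imagery effect. This follows from the text alone and needs no assumed numbers.

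**Step 2: is the contrast supplied elsewhere?** The t test on ERD and ERS maxima (Statistics) compares concentrations within each task. The permutation test concerns time-frequency maps, not accuracy. The Principal and Secondary criteria do not mention classification.

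**Step 3: illustration under assumptions.** From the document: 30 subjects, 50 trials per task, fourfold cross-validation, two-sided paired t test at 0.05. Assumed: two independent features, one shifted by MI (0 or 0.5 SD) and one by MNS (0, 0.5, 1 or 2 SD); the same effects in every subject; linear discriminant analysis in place of the named classifier; 40 replicates per row.

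Large-sample check: accuracy = Φ(D/2), with D = √(d_MI² + d_MNS²) for MI + MNS vs Rest and D = d_MI for MI + MNS vs MNS. For d_MI = 0 and d_MNS = 0.5, 1, 2: Φ(0.25) = 0.599, Φ(0.5) = 0.691, Φ(1) = 0.841. For d_MI = 0.5 and d_MNS = 1: D = √1.25 = 1.118 and Φ(0.559) = 0.712.

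Simulated mean accuracies:

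| d_MI | d_MNS | MI vs Rest | MI + MNS vs Rest | MNS vs Rest | MI + MNS vs MNS | Planned test favours MI + MNS |
|---|---|---|---|---|---|---|
| 0 | 0 | 0.503 | 0.502 | 0.500 | 0.501 | 1 of 40 |
| 0 | 0.5 | 0.497 | 0.587 | 0.588 | 0.504 | 40 of 40 |
| 0 | 1 | 0.498 | 0.687 | 0.688 | 0.500 | 40 of 40 |
| 0 | 2 | 0.499 | 0.835 | 0.835 | 0.499 | 40 of 40 |
| 0.5 | 0 | 0.585 | 0.585 | 0.499 | 0.584 | 0 of 40 |
| 0.5 | 0.5 | 0.582 | 0.629 | 0.586 | 0.587 | 40 of 40 |
| 0.5 | 1 | 0.582 | 0.704 | 0.683 | 0.584 | 40 of 40 |
| 0.5 | 2 | 0.584 | 0.844 | 0.836 | 0.587 | 40 of 40 |

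With no imagery effect, MI + MNS vs Rest matches MNS vs Rest to within 0.001. The planned test follows the stimulus. MI + MNS vs MNS stays at 0.50 without an imagery effect and at 0.58 to 0.59 with one, whatever the MNS effect.

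**The case against.** **Standing of the analysis.** Classification is in neither the principal nor the secondary criteria, and the study calls itself exploratory. This stands and lowers the severity.

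**Rest is not defined in the Statistics section**, and the article condenses a fuller protocol, so Rest might mean stimulated rest. The text does not favour this: the only resting state described follows the task, MNS alone is always named as a separate task, and one word serves both comparisons. If something else was meant, the wording still has to be corrected.

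**A reader might infer that the contrast will never be examined.** That is firmer than the text allows. The article does not list every class pair for the four classifiers, the Objectives promise to study MNS combined with intention, and the Discussion shows that the contrast is known. What can be said is that the one accuracy test named is not that contrast.

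**A reader might also infer that the planned test is bound to be significant, or that patients would receive false alarms.** Neither is supported. The result depends on MNS effects under propofol that the document does not give, and the device is described as hypothetical, with further experiments first. Nor is it a defect that the classifier paragraph names no concentration; an article can leave that detail to the full protocol.

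**The better contrast has its own bias.** MI + MNS and MNS are separate tasks in random order, with different timing and different ERD and ERS windows, and the Study design itself names fatigue and gel drying. If Rest comes from the same run as the imagery, putting MI + MNS versus MNS into the paired t test against MI versus Rest would set a between-run accuracy against a within-run one. This stands, and it is why the contrast should be added and tested against chance, not swapped in.

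**Conclusion.** The point holds. As worded, the named accuracy test confounds stimulus with intention, and a significant gain for MI + MNS versus Rest could come wholly from the stimulus. The conclusion rests on the article's own statements that MNS alone produces ERD and ERS, and on reading Rest as the unstimulated period after the task.

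The size is unknown. The simulated gains over MI versus Rest with no imagery effect, about 0.09 to 0.34 (0.587 − 0.497 = 0.090; 0.835 − 0.499 = 0.336), rest on assumed effects. They also assume no variation between subjects, no run differences and additive effects, so the 40-of-40 counts show the mechanism and do not forecast this trial.

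Severity: should-fix. The ERD/ERS amplitude analyses are not touched.

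**What to change.** 1. Add MI + MNS versus MNS alone as the accuracy analysis that addresses intention, at 0, 0.5 and 1.0 µg/ml. Align epochs on the stimulus and use the same window for both classes.
2. Test each accuracy against chance, for example by label permutation, and give a confidence interval.
3. Classify the pre-cue segments of the same runs as a negative control. Accuracy there should be at chance; if it is above chance, run differences contribute.
4. Keep MI + MNS versus Rest, and its paired comparison with MI versus Rest, as descriptive only, and state what Rest is.

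**Cost.** No new recordings: MNS alone is already planned with 50 trials at each concentration. The work is re-epoching, one more classification per concentration and the control analysis. Reported accuracy will probably be lower than against Rest. Because the two tasks are separate runs, the control must be shown and run differences acknowledged; it can flag them but does not remove them.
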